### Treatment and procedures

Patients admitted to the hospital with a proximal femoral fracture will be treated according to the treatment guidelines for proximal femoral fracture in the elderly of the Nederlandse Vereniging voor Heelkunde (Dutch trauma surgery society) [23]. A timeline with all scheduled data registrations and assessments is presented in Table 2
*.*

**Table 2 Tab2:** Timeline for scheduled procedures and assessments

Procedure/Assessment	Admission	In-hospital treatment phase	6 weeks after surgery^a^	3 months after surgery^a^	12 months after surgery^a^
*Baseline measurements*	X				
*Physical examination*	X	X	X	X	X
*X-ray assessment*	X				
*Katz ADL*	X		X	X	X
*EQ-5D*	X		X	X	X
*6CIT*	X		X	X	X
*SNAQ*	X				
*VAS pain*		X	X	X	X
*Complication* ^*a*^ *registration*		X	X	X	X
*Mobility tests* ^*b*^			X	X	X

^a^Any patient reported complication in the previously described surgical and non-surgical complication list and any reason for a postoperative readmission to a hospital

^b^HHS, SPPB, TUG, FAC

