### Objective

The aim of this study is to compare hip function, postoperative complications and patient mobility after hemiarthroplasty via the anterior or lateral approach for a displaced femoral neck fracture in elderly patients.

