#### Secondary outcomes

##### Clinical outcomes

Surgical parameters: mean operation time (skin-to-skin), mean total blood loss.Surgical complication rates (postoperative bleeding,^1^ haematoma formation, implant failure, implant dislocation,^2^ implant luxation, femoral head necrosis, periprosthetic fractures,^3^ superficial wound infection,^4^ deep wound (prosthesis) infection,^5^ nerve damage^6^).Cognitive status measured with the 6CIT score [12, 13] at admission to the hospital and at 6 weeks, 3 months and 12 months after surgery, and DOS scores during admission [14].Duration of hospital stay, cause of delayed discharge (considered later than 72 h after surgery), discharge destination and duration of rehabilitation (in days).Readmission and operative revision rate.1-year mortality.^7^
Non-surgical complications up to 12 months after surgery (delirium,^8^ anaemia,^9^ cardiac complications (decompensation and ischemia), CVA, pressure sores,^10^ electrolyte disturbances, pulmonary embolism,^11^ pneumonia,^12^ renal failure, sepsis,^13^ deep venous thrombosis^14^ and urinary tract infections^15^).Functionality and balance through a series of physiotherapeutic tests (Short Physical Performance Battery [15], Timed Up and Go test [16], Functional Ambulatory Categories [17]) at 6 weeks, 3 months and 12 months after surgery.Pain measured using a visual analogue scale (VAS) during in-hospital treatment and at 6 weeks, 3 months and 12 months after surgery.Patient-reported performance in activities of daily living using the Katz ADL Index [18] at 6 weeks, 3 months and 12 months after surgery.Health-related quality of life using the EQ-5D questionnaire [19, 20] at 6 weeks, 3 months and 12 months after surgery.

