#### Postoperative procedures

Postoperative patients are visited daily by a surgical resident and discussed twice a week by a multidisciplinary team including an orthopaedic trauma surgeon, ward doctor, trauma nurse, physiotherapist, dietician, geriatrician and transfer nurse. In our study hospital, hip fracture patients are preferably discharged 3 days after surgery according to local protocol. Patients are discharged home if pain is manageable, no active complications are present, and if mobility is adequate for living independently (meaning that the patient can safely make indoor transfers) or if home care is available and sufficient. If home care is not sufficient, discharge to one of the nursing homes specializing in hip fracture rehabilitation is planned. These assessments are also made by the multidisciplinary team for all patients twice a week. All patients fit for rehabilitation will be invited for outpatient check-ups 6 weeks, 3 months and 12 months after surgery. The reasons for failure to follow up will be recorded.

The outpatient check-ups include consultations by a trauma surgeon or surgical resident, a physiotherapist for mobility assessments and a geriatrician for strength and balance assessments and osteoporosis screening and treatment. A timeline with the scheduled procedures and assessments is presented in Table 2.

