### Ethical considerations and safety

Patient data will be handled according to the Good Research Practice guidelines. Data will be registered directly and simultaneously with the digital patient files and during oral questionnaires. Data will be registered anonymously in the database to ensure confidentiality. The identification code list will be safeguarded by the principal investigator.

All patients will be treated according to regular protocol in the study hospital. Participation in this observational study will not pose any additional risks for patients and does not influence their treatment in any way. All patients will be given the explicit opportunity to withdraw their data from the study. No individual participant’s data will be published and no informed consent for participation will be collected from the patients. This study was approved by the institutional Medical Research Ethics Committee (METC Southwest Holland; protocol number 16–059). The results of the study will be published in a peer-reviewed medical journal.

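### After discharge, complications are registered by patient report and readmission reason, which does not match a 12-month window that includes laboratory-type events and delirium

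*Protocol article*

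**What the plan says.** The Objective section of the protocol article sets out to "compare hip function, postoperative complications and patient mobility after hemiarthroplasty via the anterior or lateral approach". Complications are therefore part of the stated aim, although they are listed as secondary outcomes.

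Under Clinical outcomes the horizon and the list are given: "Non-surgical complications up to 12 months after surgery (delirium,^8^ anaemia,^9^ cardiac complications (decompensation and ischemia), CVA, pressure sores,^10^ electrolyte disturbances, pulmonary embolism", followed by further items that include renal failure, pneumonia, sepsis and urinary tract infection.

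Table 2 (Treatment and procedures) marks complication registration in hospital and at 6 weeks, 3 months and 12 months. Its footnote says what is registered: "Any patient reported complication in the previously described surgical and non-surgical complication list and any reason for a postoperative readmission to a hospital".

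Other statements bear on how events come to light:

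- Cognition is tested at admission and again "at 6 weeks, 3 months and 12 months after surgery, and DOS scores during admission".
- In hospital, "Postoperative patients are visited daily by a surgical resident and discussed twice a week by a multidisciplinary team" (Postoperative procedures).
- After discharge, "The outpatient check-ups include consultations by a trauma surgeon or surgical resident, a physiotherapist for mobility assessments and a geriatrician" (same section). The geriatrician's stated tasks are strength, balance and osteoporosis.
- On data sources: "Data will be registered directly and simultaneously with the digital patient files and during oral questionnaires" (Ethical considerations and safety).
- The sample size section anticipates 40% failure to follow up. The section on postoperative procedures adds that the reasons for it will be recorded.

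**The concern.** The outcome definition and the capture rule do not fit each other after discharge. Anaemia, electrolyte disturbance and renal failure are usually recognised from blood results, and delirium by an observer. The patient is a weak source for all four. If such an event does not lead to readmission, the footnote leaves it to the patient to mention it at a visit. A patient who has died or does not attend cannot mention anything, and such patients may well be the ones who had complications.

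What is at stake is the comparison of later complications between the two approaches. Missed events cost information and shrink an absolute difference. If attendance or recall differs between the cohorts, the comparison can also shift in either direction. The propensity score is built from baseline parameters, so it does not correct for unequal capture after surgery.

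**Working it through.** **Step 1. Events and means of detection, as the article states them.**

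| Period | What could reveal a complication |
|---|---|
| Index admission | DOS scores for delirium, daily visits by a resident, team discussion twice a week, physical examination |
| After discharge, readmitted | reason for readmission (footnote) |
| After discharge, not readmitted, attends | patient report (footnote); physical examination; 6CIT |
| After discharge, not readmitted, does not attend or has died | nothing stated for complications other than death itself |

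Physical examination does not measure haemoglobin, electrolytes or renal function. The 6CIT is a cognition score at one moment and would not show a delirium that came and went between visits. The gap lies in the last two rows.

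**Step 2. The plan's own attrition figure.** 41 / (1 − 0.40) = 68.3, rounded up to 69 per group, 138 in total, as stated. The plan thus allows for 69 − 41 = 28 patients per group, 56 of 138, without complete 12-month follow-up. (How the 41 was reached does not matter here.)

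**Step 3. What this means for patient report.** An event between the 3-month and 12-month visits that causes no readmission can be reported only at the 12-month visit. Suppose that the 40% applies to that visit and that attenders and non-attenders have the same event risk (both assumptions). Then

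capture s = attendance × recall

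| Recall among attenders (assumed) | s | True difference of 10 points (assumed) appears as |
|---|---|---|
| 1.00 | 0.60 × 1.00 = 0.60 | 6 points |
| 0.75 | 0.60 × 0.75 = 0.45 | 4.5 points |
| 0.50 | 0.60 × 0.50 = 0.30 | 3 points |

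This counts a patient with no report as event-free. If only attenders are analysed, the loss becomes a selection problem instead.

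**Step 4. Effect on the comparison, equal capture in both cohorts.** Take assumed true risks of 30% and 15% with 69 per group. At s = 0.60 the observed risks are 18% and 9%.

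- Risk difference: 15 points becomes 0.60 × 15 = 9 points.
- Risk ratio: 30/15 = 2 and 18/9 = 2, unchanged.
- Odds ratio (the article plans logistic regression for binary outcomes): (0.30/0.70)/(0.15/0.85) = 2.43 becomes (0.18/0.82)/(0.09/0.91) = 2.22.
- Power of a two-sided comparison at 5%: 56% becomes 34%.

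Equal under-capture therefore costs mainly precision and absolute difference, and relative measures little.

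**Step 5. Unequal capture.** With the same true risk of 30% in both cohorts and capture of 60% against 45% (assumed), the observed risks are 18% and 13.5%, a spurious difference of 0.30 × (0.60 − 0.45) = 4.5 points. The documents do not show whether capture would differ, or in which direction.

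**Limit of steps 3 to 5.** They apply to post-discharge events without readmission. The observed total difference is the in-hospital difference plus s times the post-discharge difference, and the article does not give the split between the two.

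**The case against.** The strongest case is that the footnote is being read too literally.

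- **Inpatients are observed.** DOS scores, daily visits and the multidisciplinary team cover the admission. The footnote marker also stands on the three follow-up headings and not on the in-hospital heading. This stands. A reader might infer that delirium is measured nowhere, or that inpatient complications wait for the patient to report them; the article does not support either.
- **Patient files are a data source.** This stands in part. The sentence on ethics says that data are registered simultaneously with the files. It does not say that complications are extracted from them for every patient, including those who stay away. If that is what is meant, the footnote says something else and the two need reconciling.
- **Table 2 is not exhaustive.** DOS scores and osteoporosis screening take place but have no row. This stands, so the lack of a laboratory row does not prove that no blood is taken after surgery. It does not supply a capture rule for results that may exist.
- **Patients can pass on a diagnosis.** This stands, and the definitions behind the complication footnotes are not shown. It would be too strong to say that these events cannot be reported, or that all are defined by a laboratory value. They cannot be relied on to be reported.
- **The capture rates are invented.** This stands. None comes from the documents, so the figures above show how the mechanism works and do not estimate the bias.

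**Conclusion.** The point holds for the period after discharge. As written, the rule does not reliably capture events that cause no readmission, or events in patients who die or miss visits, and what it does capture depends on attendance and recall. The plan's own 40% shows that attendance is not a marginal matter.

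The size is unknown. The illustrations rest on assumed risks, assumed recall, and the 40% applying to the 12-month visit with equal risk in non-attenders. A reader might conclude that a finding of no difference in complications would be uninterpretable. That does not follow: in-hospital events are observed directly, readmissions are covered, and equal under-capture leaves the risk ratio unchanged.

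The matter is of modest weight. Complications are secondary, and neither the Harris Hip Score nor the sample size is affected. It is worth correcting because complications are a named aim and the correction is cheap.

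**What to change.** Reword the Table 2 footnote so that complications, readmissions and revisions are taken from the digital patient file at the same fixed dates for every operated patient in both cohorts, whether or not the patient attends. Keep patient report as a supplement, and note the source of each event. Bring the footnote into line with the 12-month window under Clinical outcomes and with the statement on patient files in the ethics section.

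Report delirium and the laboratory-based items (anaemia, electrolyte disturbances, renal failure) separately for the index admission and for the time after discharge. Limiting them to the admission would throw away planned outcome data; separate reporting keeps the later period and shows that it is measured less well.

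The cost is one chart check per patient at the fixed dates, in files the team already uses, and a change of wording. No extra visit is needed. The remaining weakness is that events treated only elsewhere still depend on patient report.

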#### Preoperative procedures

In accordance with standard care, X-ray examinations of the pelvis, hip and thorax are made on admission and assessed by the radiologist and orthopaedic trauma surgeon. After diagnosis all patients will receive an information brochure about the standard care (treatment and rehabilitation) of the study hospital. All patients are screened for osteoporosis and treated if necessary.

At this stage, registration of patient data will be performed by the physician on call in the emergency department (ED) and the ED nurse. The baseline questionnaires (including the SNAQ and Katz ADL and the EQ-D5) are registered by a proficient nurse upon arrival on the surgical ward before surgery.

#### Surgical procedures

Surgery will be performed by experienced surgeons in accordance with the national surgical treatment protocol for proximal femoral fracture of the Nederlandse Vereniging voor Heelkunde (Dutch trauma surgery society). The choice of a specific surgical approach will depend on the experience of the surgeon on call: all surgeons use the approach they are most familiar with. The group consists of 16 highly experienced orthopaedic trauma surgeons. Residents with insufficient experience to perform the operation independently, operate under strict supervision of the trauma surgeons. The LA and DAA are standard approaches for hemiarthroplasty in the study hospital.

Patients are operated as soon as possible after full medical check-up (including laboratory tests, physical examination and consultation by a geriatric specialist) and anaesthesiological approval.

The prosthesis used will be the self-centring, 3-point-contact anchorage cemented CCA straight stem prosthesis in accordance with [name] in a standard of lateral version combined with a short or medium hemiprosthesis head produced by of Mathys Medical®. Patients with a severe history of cardiovascular diseases with pump failure or hypotension during operation are at risk of adverse events associated with bone cement implantation syndrome and are excluded from the study and treated with an uncemented prosthesis. This is assessed and decided subjectively by the treating anaesthesiologist and trauma surgeon.

The anterior approach will be performed with the patient in a supine position. An incision of about 15 cm is made in a straight line starting two fingers lateral and caudal of the spina iliaca anterior superior heading towards the lateral side of the patella. The fascia is dissected between the m. tensor fascia lata and the m. sartorius. Using blunt dissection of the intermuscular space, the crossing vessels are cauterized and dissected. The capsule is excised to expose the joint. After completion of the procedure, the wound is closed in layers.

The lateral approach is performed with the patient in a lateral position. An incision is made starting 8 cm distal of the tip of the greater trochanter upwards to the tip and 5 cm proximally of the tip in a slightly dorsal direction, exposing the fascia lata. The fascia lata is split and retracted to expose the insertion of the m. gluteus medius which is dissected with or without vastogluteal continuity. A T-shaped incision is made in the capsule to expose the hip joint. After completion of the procedure, the capsule is closed and the wound is closed in layers.

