### Sample size

Reported one-year postoperative results for the HHS in hemiarthroplasty patients vary between 68 (standard deviation [SD] 20 [24] and 78 (SD 10) [25]. Long-term (12 months) postoperative HHS results for specific surgical approaches are lacking in literature. For the sample size calculations a difference in functionality of 10 points as measured by the HHS was considered clinically relevant [26], with a standard deviation of 15. To detect this difference two equally sized cohorts of at least 41 patients with a complete 12 months follow-up are necessary (α = 0.05, power = 80%). Anticipating failure to follow up of 40%, inclusion of at least 69 patients per intervention group, or 138 in total, is required.

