### Statistical analysis

Demographic and clinical characteristics of the cohorts will be described using summary statistics and will be compared by univariate analysis. Categorical variables will be compared using the chi-squared test if the data are sufficiently large (expected cell counts >5) or the Fisher’s exact test if this requirement cannot be met. Continuous variables will be compared by unpaired t-tests for normally distributed data, and by the Wilcoxon rank sum test for not normally distributed data.

Outcome parameters will be compared univariably between cohorts, but correction for confounding factors is of major importance because the patients in this study are not randomized. Since the number of study participants is limited relative to the number of potential confounders, a propensity score will be calculated from the available baseline parameters. The propensity score will be used to adjust for differences between the two cohorts in multivariable linear regression analyses for continuous outcome parameters and in multivariable logistic regression analyses for binary outcomes. Repeated outcome measures such as the HHS and pain score will also be analysed using Generalized Linear Models. *P*-values <0.05 will be considered statistically significant. All statistical analyses will be performed using IBM SPSS Statistics version 20.0 or higher.

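### The on-call surgeon decides the approach (16 surgeons), yet sample size and models treat patients as independent: if surgeons differ, the intervals are too narrow, and no model can separate surgeon skill from approach

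*Protocol article*

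**What the plan says.** Protocol article, Surgical procedures: the approach depends on who is on call, and "all surgeons use the approach they are most familiar with". The pool is stated: "The group consists of 16 highly experienced orthopaedic trauma surgeons". Trainees also operate: "Residents with insufficient experience to perform the operation independently, operate under strict supervision of the trauma surgeons". The Abstract and the Discussion describe the same mechanism, and the Discussion presents it as a reflection of everyday practice.

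Sample size: "a difference in functionality of 10 points as measured by the HHS was considered clinically relevant", "with a standard deviation of 15", and "two equally sized cohorts of at least 41 patients with a complete 12 months follow-up are necessary" at α = 0.05 and 80% power. The only inflation is for 40% loss to follow-up, which gives 69 per group and 138 in total.

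Statistical analysis: chi-squared or Fisher tests, unpaired t-tests or Wilcoxon tests, then adjusted models: "The propensity score will be used to adjust for differences between the two cohorts in multivariable linear regression analyses for continuous outcome parameters", with logistic regression for binary outcomes. Repeated measures such as the HHS are also to be analysed with Generalized Linear Models. No surgeon effect, clustered standard error or design effect is stated.

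Baseline parameters: the surgeon's experience level is listed and so is available to the propensity score. The surgeon's identity is not listed.

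**The concern.** Exposure is set at the level of the surgeon, but the analysis is at the level of the patient. Two separate consequences follow.

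**Precision.** Patients of the same surgeon share technique, supervision and habits. If this makes their outcomes alike, the variance of the approach contrast contains a between-surgeon part that the planned tests and regressions leave out. Intervals are then too narrow, the 5% error rate is not held, and the power of a valid analysis is below what independence implies.

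**Interpretation.** If each surgeon uses only one approach, a difference in skill between the two sets of surgeons looks exactly like an effect of approach. A propensity score balances the measured baseline variables it contains. Experience level brings in one surgeon characteristic, but it does not stand for everything that differs between surgeons.

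**Working it through.** **1. The plan's own figure.** Inputs from Sample size: difference 10, SD 15, two-sided α = 0.05 (sidedness is not stated), power 80%.

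n per group = 2 × 15² × (1.960 + 0.842)² / 10² = 35.3, so 36; the exact t-test gives 36.3, so 37. The stated 41 is not reproduced. With 41 per group and independent patients, the t-test has 84.7% power. The dropout step does reproduce: 41 / 0.60 = 68.3, so 69 per group and 138 in total. The surplus of 41 over 36.3 absorbs a design effect of 41 / 36.3 = 1.13. Nothing in the article labels it as an allowance for clustering.

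**2. Design effect.** Number of surgeons: 16 (Surgical procedures). Completers: 2 × 41 = 82, so m = 82 / 16 = 5.125 per surgeon. Assumptions, not in the documents: surgeon ICC 0.01 to 0.10, 8 surgeons per approach, equal caseloads.

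- DE = 1 + (m − 1) × ICC
- True SE / naive SE = √DE
- Actual error rate of a nominal 5% test = 2 × [1 − Φ(1.96 / √DE)]
- Power from the noncentral t with noncentrality 10 / [15 × √(2 × DE / 41)], on 80 df (82 patients − 2) or 14 df (16 surgeons − 2)

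| ICC | DE | SE ratio | Type I error | Power, 80 df | Power, 14 df |
|---|---|---|---|---|---|
| 0 | 1.00 | 1.00 | 5.0% | 84.7% | 80.1% |
| 0.01 | 1.04 | 1.02 | 5.5% | 83% | 79% |
| 0.02 | 1.08 | 1.04 | 6.0% | 82% | 77% |
| 0.05 | 1.21 | 1.10 | 7.4% | 77% | 72% |
| 0.10 | 1.41 | 1.19 | 9.9% | 71% | 66% |

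The row for ICC 0 separates two effects: 84.7 − 80.1 = 4.6 points of the power gap come only from moving to 14 df and are not a cost of clustering. On 80 df the surplus in 41 keeps power at 80% until DE reaches 1.13, that is ICC = 0.13 / 4.125 = about 0.03.

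**3. Departures from the even layout.** The article does not say how many of the 16 surgeons use each approach. With 41 completers per group spread over k and 16 − k surgeons, DE is the mean of 1 + (41/k − 1) × ICC and 1 + (41/(16 − k) − 1) × ICC. At ICC 0.05:

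- 4 vs 12 surgeons: DE 1.29, type I error 8.5%
- 2 vs 14 surgeons: DE 1.54, type I error 11.4%

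Uneven caseloads act in the same direction, through DE = 1 + [(1 + CV²) × m − 1] × ICC. With an assumed CV of 0.6 and ICC 0.05, DE = 1 + (1.36 × 5.125 − 1) × 0.05 = 1.30, and the type I error is about 8.5%.

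**4. Outcomes seen in all patients.** Operation time and blood loss do not depend on follow-up, so m = 138 / 16 = 8.6. The type I error is then 5.9% at ICC 0.01 and 14.0% at ICC 0.10 in the even layout.

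**The case against.** The strongest reply is that the size of the problem is assumed. The documents give no surgeon ICC, surgeon split or caseload. At ICC 0.01 to 0.02 the standard error is only 2% to 4% too small, the error rate is 5.5% to 6.0%, and the surplus in the 41 keeps power above 80% with patient-level degrees of freedom. This stands. A reader might infer that the standard errors are certainly wrong, or that the trial is clearly underpowered; the documents support neither. The surplus does not, however, protect the type I error.

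Second, preferring one approach does not exclude occasional use of the other, and supervised residents operate, so nesting may be incomplete. This also stands and would soften the problem. It cannot be checked without a surgeon identifier.

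Third, patients arrive according to the on-call rota, and the article gives no reason why case mix should differ by surgeon. Measured case mix is in any case what the propensity score addresses, so a claim of case-mix imbalance between surgeons has no support here. Experience level is also available to the score, so surgeon differences are covered in part.

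Fourth, a condensed article may leave the standard-error method to a fuller document. That carries less weight here, because the article itself sets out the assignment mechanism, the sample size and the models, and these do not fit together.

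Finally, the Discussion already says that results reflect each team using its familiar approach. That comes close to the right interpretation, but it is offered as a strength and is not treated as a source of clustering or confounding.

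**Conclusion.** The point holds as a mismatch between how approach is assigned and how the data are to be analysed, and it should be fixed. Its size depends on assumptions. For a surgeon ICC of 0.01 to 0.10, 8 against 8 surgeons and equal caseloads, the actual error rate is about 5.5% to 9.9%. Power for 10 points is about 83% to 71% on patient-level degrees of freedom, or 79% to 66% on 14. An uneven surgeon split or uneven caseloads make it worse; an ICC near zero makes it negligible.

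It would be tempting to conclude that a surgeon term cures the whole problem. It does not. With surgeons nested in approach, a fixed surgeon effect cannot be estimated alongside approach. A random intercept or clustered error corrects the precision but leaves surgeon skill and approach confounded. That part can only be met by how the conclusion is worded.

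**What to change.** 1. Record a coded identifier of the responsible surgeon for every patient, using the supervising surgeon when a resident operates. The article does not list this variable, so it should be confirmed as captured now; recovering it later may not be possible.
2. Report the number of surgeons and of patients per approach, and any surgeon who used both.
3. Fit the propensity-adjusted linear model and the repeated-measures models with a random surgeon intercept and Satterthwaite or Kenward-Roger degrees of freedom, or use cluster-robust errors with a small-sample correction. For binary outcomes use GEE or cluster-robust errors, again with a small-sample correction for 16 clusters.
4. Restate the power of the planned 41 completers per group over a stated ICC range, with the degrees of freedom given.
5. Word the conclusion as the effect of each approach as delivered by surgeons who prefer it, and name confounding by surgeon skill as a limitation.

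Cost: one more recorded variable, some analysis text, wider intervals and a lower stated power. No additional patients are asked for.
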